# A collaboration between service users and professionals for the development and evaluation of a new program for cardiovascular risk management in persons with a diagnosis of severe mental illness: French multicenter qualitative and feasibility studies

**DOI:** 10.1186/s13033-019-0331-6

**Published:** 2019-12-27

**Keywords:** Cardiovascular disorders, Mental health, Empowerment, Health promotion, Public health

## Abstract

**Background:**

Persons with a diagnosis of severe mental illness have a life expectancy that is 20 years lower than the general population, and they are disproportionately affected by cardiovascular disorders. Improving the management of cardiovascular risk is one of the main challenges for the public health system. In the care pathway of persons with a diagnosis of severe mental illness, a better understanding of limiting and facilitating factors is required. The objective was to include persons with a diagnosis of severe mental illness, carers, and primary and mental health professionals in the creation and evaluation (feasibility) of a health promotion program designed to improve cardiovascular risk management through empowerment.

**Methods:**

This study combines a mixed methodology with qualitative and quantitative components. A multicenter prospective qualitative study was conducted in seven mental health units in France and was coordinated by a steering committee composed of persons with a diagnosis of severe mental illness, carers, and primary and mental health professionals.

**Results:**

This health promotion program must enable persons with a diagnosis of severe mental illness to assert their right to self-determination and to exercise greater control over their lives, beyond their diagnosis and care. Following a preliminary feasibility study, the effectiveness of this new tool will be evaluated using a randomized controlled trial in a second study.

**Conclusions:**

The findings can be used by health organizations as a starting point for developing new and improved services for persons with a diagnosis of severe mental illness.

*Trial registration* Clinical Trials Gov NCT03689296. Date registered September 28, 2018

## Background

In France, it is estimated that 4 million persons have some form of severe mental illness [1]. Persons with a diagnosis of severe mental illness (SMI) have a life expectancy that is 20 years lower than the general population, even after excluding suicide and accidents as the cause of death [2]. In addition, studies show that 19–57% of persons with SMI have at least one associated physical condition, including cardiovascular, gastrointestinal, respiratory, neoplastic, infectious, endocrine, and oral disorders. It is estimated that half of these comorbid conditions are undiagnosed [3, 4].

Unequal access to health services and quality of care are among the main reasons for the reduced life expectancy in individuals with SMI. As a result, cardiovascular risk factors (CVRF) are more frequent, regardless of the mental health diagnosis. For example, persons with SMI are 1.5–2 times more likely to have diabetes, dyslipidemia, hypertension, and obesity the general population [3], and they are less likely to undergo revascularization procedures after a myocardial infarction [5]. When seeking care, they may also be subject to discriminatory practices as a result of stigma and lack of communication skills [6]. This neglect in management and prevention of health problems is usually described by professionals as a result of the mental disorder or the side effects of medication [6, 7].

CVRF are a major cause of death in France, with nearly 150,000 deaths per year, representing more than 25% of all deaths [1]. The circumstances for the onset of CVRF depend mainly on age, lifestyle-based risk factors and environmental conditions, potentiating individually acquired or familial genetic susceptibilities (obesity, hypercholesterolemia, type 2 diabetes, high blood pressure).

It has been established that medical care accounts for only 10–20% of modifiable health factors [8], and, as a result health, strategies focus primarily on promoting positive health behaviors and limiting behavioral risk factors at all ages (tobacco, diet, and sedentary lifestyle in particular) through their identification and appropriate management [3]. This type of strategy was highlighted by the World Health Organization (WHO) in 2016 at the 9th Global Conference on Health Promotion [9], in accordance with the United Nations (UN) Sustainable Development Goals (SDG) agenda [10].

Worldwide, the occurrence, importance, and gravity of physical disorders have long been underestimated for individuals with SMI. In France, progress has been made under the combined pressure of clinical evidence, health professionals, and patient actions and organizations. However, recent studies show the gap in life expectancy between the general population and persons with SMI has continued to widen in France [11] and worldwide [12].

This observation led the WHO to define the promotion of physical health of individuals with SMI as one of the priorities of the 2013–2020 European Mental Health Plan [13], and a recent report from the 2020–2030 UN SDG agenda builds on this objective [14].

In recent years, there has been an increased recognition of the experiential knowledge of health care users [15] and their ability to adapt professional knowledge to the requirements of everyday life. In this model, health decisions are not based on the opinions of professionals but on service users’ right to self-determination regarding their health. This is in line with the orientation of UN and WHO policies towards a human rights-based approach [16]. Strategies based on the empowerment concept have been developed to enhance experience and rights of health care users.

This concept strives to shift the existing balance of power between individuals, groups, services, and governments [17]. At the collective and organizational level, empowerment aims to redefine the health care system and transform it into a learning organization that promotes change. It involves a change in attitudes, policies, training, and methods of providing care, including mental health care. Service users are thus in a position to manage their own “health capital”, to acquire certain rights, and to have a recognized central position in the organization of healthcare. Empowerment is becoming a fundamental concept in health promotion. It aims to increase the power to act and the ability to steer one’s own life in the medical and social spheres. It is a shift from a paternalistic and stigmatizing approach to emancipatory and rewarding dynamics [18, 19]. Thus, several perspectives can be considered: a clearer view of oneself and one’s ill health, better use of the healthcare system’s support services, improved management of life changes, and finally, more deft use of adjustment strategies to integrate ill health and therapy into one’s daily life [20–22].

Both individuals with a mental health disorder and their carers have expressed a willingness to share their experience, the difficulties they have encountered, and the strategies they have developed to limit the effects of social isolation and stigma. They have also expressed a desire to develop new strategies for coping and building confidence and self-esteem during times of hardship. It has been shown that a peer exchange process promotes identity building through individual and collective redefinition of the experience of mental health problems and re-appropriation of the health experience, available support and recommended therapeutic strategies [22]. In addition, health support initiatives tend to reinforce active and responsible health behavior. The redefinition of the health care user as a “patient-actor” requires individuals to engage in meaningful participation in decisions that affect them and to develop a practical approach to health care [21].

In parallel, health professionals must take into account the experience of individuals with a mental health disorder and avoid monopolizing health-related decisions [15, 16, 22]. A current challenge within the public health system is to expand the understanding of the factors that limit and facilitate the healthcare pathway for persons with severe mental disorders in order to improve the management of CVRF. The reasons for which health care consumers, carers and health professionals do not work together on this issue are still to be fully explored.

The main objective of this study is to use data from focus groups (FG) to develop and evaluate (feasibility) a health promotion program to encourage the physical health of individuals with severe mental illnesses through a reduction of CVRF.

## Study design and methods

### Study design

This is a mixed methodology research project that combines qualitative and quantitative studies.

First is a prospective multicenter exploratory phase conducted in 7 mental healthcare facilities in France. These institutions are all members of a health cooperation group coordinated by the EPSM-Lille-Métropole—WHO Collaborating Centre for Research and Training in Mental Health.

The multicenter exploratory phase will be composed of three steps: (1) creation of a steering committee, (2) creation of the interview guide, and (3) construction of a health promotion program.

Next, a feasibility study will be carried out at La Chartreuse Hospital (Dijon, France) to test the health promotion program.

This research is based on a growing body of evidence that including individuals whose expertise lies in their personal experience not only improves the studies themselves, but also their implementation in day-to-day practice [23]. Several measures have been taken to facilitate the effective participation of those directly concerned, including the use of language consistent with the UN Convention on the Rights of Persons with Disabilities and recommendations from persons with disabilities [24].

Both health care users and carers are involved at all stages of the project, from early design to implementation and data analysis. In addition, at least one person who has experienced a diagnosis of severe mental illness and who is familiar with the French health system is involved at all stages of the study process. As members of the steering committee, users and carers will be equally represented and have the same power as the other stakeholders. This organization aims to ensure their participation and consent in all decisions. Finally, they will participate in the drafting of all publications and the dissemination of results.

### Multicenter exploratory phase

#### Creation of a steering committee

The coordination of the research will be under the control of a steering committee composed of various stakeholders: primary care professionals, mental health professionals, carers, health care users, public health and sociology researchers, and health promotion and education specialists. The operating rules of this committee allow for equal representation of each group of stakeholders, and require that decisions be taken unanimously.

The day-to-day management of the study will be monitored by the steering committee. The committee will meet at least annually or more frequently if required.

#### Creation of an interview guide for the construction of a health promotion program

An exploratory phase including individual interviews at the beginning of the study will be used for the creation of a collective ad hoc interview grid. The steering committee will develop specific interview guides for the FGs of the health care users, carers, primary care professionals, and mental health professionals. The guides will be based on results from an exploratory study (about 5–7 individual semi-structured interviews) and a review of relevant scientific literature. The collective interview guide will cover different aspects of health promotion for persons with SMI including views, experiences and representations of CVRF, the acceptability of care and the care pathway. For each group of interviewees, the main focus will be factors that limit or facilitate the healthcare pathway for individuals with SMI. The objective is to improve the management of CVRF. Interview guides will be tested before being used for data collection, and will be subjected to amendments as necessary after deliberation of the SC.

#### Construction of the health promotion program

Starting from the reality of the field and the psychosocial determinants of CVRF, FGs will be used to favor the inductive and abductive approach [25]. This method takes precedence over other qualitative methods for this particular study as it allows in-depth examination of the phenomenon, ensures participant confidentiality and enables pre-specified topics to be explored while opening up to the possibility of other ideas and thoughts that may spontaneously arise in group conversation. FGs will be conducted separately with each group: health care users, carers, primary care professionals (general practitioners, nurses, dentists, pharmacists), and mental health professionals.

This phase will be used to define the set of most relevant CVRF for all participants (which will therefore be included in the health promotion program), the number of educational techniques to be used (traditional lectures, discussions, simulated games, computer technology, written material, audiovisual sources, verbal recall, demonstration, and role playing), as well as the evaluation strategy for the program. A questionnaire will also be created to record any changes in the representations of CVRF for the feasibility study before and after the implementation of an educational programme. At each step of the study, the sociologist leading the FGs will be asked to provide expert advice.

### Feasibility study

When the health promotion program is finalized by the SC, a prospective, monocentric, non-comparative implementation trial will be set up in one study center (Chartreuse Hospital, Dijon). The purpose of this trial will be to evaluate the best course of action and the most relevant method of assessing the program’s impact on CVRF in a future randomized controlled trial, and to assess the potential transferability of the newly constructed health promotion program.

The flow chart is shown in Fig. 1.

**Fig. 1 Fig1:**
[figure not shown]
Study flow diagram

## Methods

### Construction of a health promotion program

#### Sample

The number of participants included in the construction of health promotion program is defined by the threshold of concept saturation [26, 27]. We aim to have 30 subjects per group, totaling 120 subjects for the four FGs. With an estimated maximum refusal rate of 30%, a pool of 160 candidate participants will be required [26, 27]. In the event of secondary refusals in view of the progress and/or schedule of the FGs, the missing participants will be replaced. Data regarding refusals and the reasons for these refusals will be collected.

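### At the stated maximum refusal rate of 30%, a pool of 160 candidates is expected to yield about 112 focus-group participants, not the target of 120; 160 suffices only if refusal is 25% or less

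*Protocol article*

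**What the plan says.** The relevant text is the Sample paragraph under Methods, Construction of a health promotion program, in the protocol article. It bases the number on saturation: "The number of participants included in the construction of health promotion program is defined by the threshold of concept saturation". It then gives a numerical target: "We aim to have 30 subjects per group, totaling 120 subjects for the four FGs". The next sentence sizes the recruitment pool: "With an estimated maximum refusal rate of 30%, a pool of 160 candidate participants will be required". A replacement rule follows: "In the event of secondary refusals in view of the progress and/or schedule of the FGs, the missing participants will be replaced". The paragraph ends by saying that refusals and the reasons for them will be recorded.

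The article shows no derivation of 160. It does not say how the pool is divided among health care users, carers, primary care professionals and mental health professionals.

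**The concern.** A pool that is called required under a maximum refusal rate should be large enough at that rate, and 160 is not. The target, the refusal rate and the pool size are all stated in the same paragraph, so the mismatch can be checked from the text alone and does not depend on anything the article leaves to the full protocol.

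What is at stake is a recruitment planning figure for seven centers. If they treat 160 as enough and refusal reaches the planned maximum, they should expect fewer than 120 participants and will have to go back for more candidates. Because refusals are to be recorded, the planned and actual yields will later be set side by side, and the planned one should be coherent.

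**Working it through.** **Inputs**, all from the Sample paragraph:
- target: 4 groups x 30 = 120 participants
- maximum refusal rate: r = 0.30
- stated pool: 160 candidates

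**Step 1: try to reproduce the stated pool.** If a proportion r of those approached refuse, the pool needed for n participants is n/(1 - r). With the stated inputs:

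120/(1 - 0.30) = 120/0.70 = 171.4, rounded up to 172.

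The stated 160 is not reproduced; the difference is 172 - 160 = 12. Working by group, 30/0.70 = 42.9, rounded up to 43, and 4 x 43 = 172, so the two routes agree.

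**Step 2: what 160 delivers at 30%.** 160 x 0.70 = 112. The shortfall is 120 - 112 = 8, or 8/120 = 6.7% of the target. If the pool were split equally (40 per group) and refusal were the same in every group, this would be 40 x 0.70 = 28 per group instead of 30. The article states neither condition.

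**Step 3: the refusal rate at which 160 is right.** 1 - 120/160 = 0.25. The same formula at 25% gives 120/0.75 = 160 exactly.

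| Refusal rate | Expected yield of 160 | Pool needed for 120 |
|---|---|---|
| 20% | 160 x 0.80 = 128 | 120/0.80 = 150 |
| 25% | 160 x 0.75 = 120 | 120/0.75 = 160 |
| 30% | 160 x 0.70 = 112 | 120/0.70 = 171.4, so 172 |

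**Step 4: chance variation.** Assume that each candidate accepts independently with probability 0.70. The binomial probability of at least 120 acceptances is then about 10% from 160 candidates and about 56% from 172. So 172 makes the expected yield meet the target (172 x 0.70 = 120.4) without guaranteeing it. Independence is an assumption made here and is not in the article.

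**The case against.** The strongest case on the other side concerns the consequence, since the division itself is not open to dispute.

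- **The number is not a powered sample size.** Saturation governs the sample, recruitment is purposive, and 120 is expressed as an aim. Nothing in the article suggests that a few participants fewer would prevent saturation. This stands, and it limits the point to a minor one.
- **30% is a maximum.** At 25% or below, 160 is enough. This also stands. The text nevertheless ties 160 to the 30% figure, and at that figure it fails.
- **Missing participants are replaced.** The rule shows an intention to hold the target, but it is limited to secondary refusals arising from the progress or schedule of the focus groups. It does not cover the refusals used to size the pool. Replacements must also come from candidates, so the rule adds to the number needed.

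Three stronger readings are tempting, and the article supports none of them.

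- A reader might infer that the planned sample will not be delivered. The article does not call 160 a ceiling; eligible people are identified prospectively at seven centers, and nothing prevents further approaches.
- A reader might infer that every stakeholder group ends below 30. That needs an equal split of the pool and equal refusal across four quite different groups, and the article says neither.
- A reader might infer that 160 came from adding 30% to 120, which gives 156, and rounding up. No derivation is shown and 156 is not 160, so this is conjecture, and the point does not need it.

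**Conclusion.** The sentence is wrong as written, and the error is minor. At the stated maximum refusal rate, 160 candidates are expected to yield about 112 participants, 8 below the target, unless more are approached; 172 would be needed for an expected yield of 120. The conclusion rests on one assumption, the ordinary meaning of a refusal rate as the share of those approached who decline.

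The practical effect is modest. No test, precision target or error rate depends on the 120, and the later feasibility study has its own separate sample of 30. This is a correction to a planning statement and does not call the design of the qualitative phase into question.

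**What to change.** Any one of three changes to the Sample paragraph makes the figures agree:

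1. Keep the target of 120 and the 30% maximum, and restate the pool as 172 candidates (43 per group if split equally).
2. Keep the pool of 160 and state that it covers refusal of up to 25%.
3. Keep 160 and 30%, and state that the expected yield at that rate is about 112, with further candidates to be approached if saturation calls for them.

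The first costs at most 12 more approaches, 3 per group if split equally. The second and third change only the wording. None affects the qualitative analysis or the feasibility study.

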#### Eligibility

For all four groups, included participants will be over age 18 and not in a mental health crisis at the time of the study. Informed consent will be obtained from each participant and from their legal guardians for persons under guardianship. Due to the qualitative study design, persons with poor French language skills will not be included in this stage. Health care users, carers, and health professionals are required to have a personal/caring/professional experience of a long-term mental health problem. Persons with SMI are considered by the French health care system as having a long-term illness. The criteria for this classification include having a mental health problem for more than a year, and having received a diagnosis of mental illness according to the WHO ICD-10. As such, these patients benefit from an exemption from user fees and a 100% reimbursement of their health costs (excluding cost overruns). While official data on the diagnosis of affective disorders is lacking, approximately 6 in 1000 people in France are declared as having a long-term condition for psychosis [1]. Interviewees will be recruited following a mixed purposive sampling strategy, including maximum variation, extreme and/or deviant cases. Maximum variation sampling will consider each participant’s age, gender, level of education, history of CVRF and lifestyle (for users and carers) and length of professional experience and place of practice (for primary care and mental health professionals).

#### Recruitment procedures

Recruitment will be on a voluntary basis. As a result, there is no pre-selection of participants who meet the eligibility criteria.The identification of eligible persons will be carried out prospectively by the principal coordinator of the study from one of the centers participating in the study. Health care users will be recruited from both outpatient and inpatient activity of the participating centers.Carers included in the study are defined as adults helping a person with a mental health problem that has been recognized as a long-term illness. They will be recruited with the mandatory agreement of service users.Primary care and mental health professionals (private practice or hospitals) will be identified through reports sent by participating centers.

Participants will be asked to complete a consent form for this phase of the non-interventional study.

